### 2.8. Data Collection and Timing

Recruitment strategy

Participants are recruited consecutively from patients scheduled to undergo PICC or PICC-PORT placement at the hospital where the study is conducted. Screening for eligibility, based on the predefined inclusion and exclusion criteria, is performed on the day of the procedure by a member of the study nursing team. Eligible patients are then approached prior to entry into the procedural room or outpatient surgical area, provided with detailed study information and invited to participate. In the case of a positive response, written informed consent is obtained.

Based on institutional activity in 2024, with an average of approximately 15–20 PICC/PICC-PORT insertions per week, a recruitment rate of around 8–10 patients per week can be conservatively anticipated. Accordingly, the target sample size of 120 participants is expected to be reached within approximately 10–12 weeks of active, continuous recruitment. Participant flow through the study will be documented using a CONSORT-compliant flow diagram, anticipated to guide reporting of the main trial results [22].

Data are collected at two predefined time points using a structured case report form specifically developed for the study and subsequently entered into the REDCap electronic database, Figure 1.
T0 (pre-procedural): within 2 min of room entry and prior to preparation of the sterile field, baseline procedural anxiety, pain intensity and physiological parameters (heart rate and arterial blood pressure) are recorded.T1 (post-procedural): within 2 min of completion of the procedure, after removal of the VR headset (for the intervention group) and before the patient leaves the procedural room, patient-reported outcomes related to procedural experience and satisfaction are collected, together with brief qualitative questions exploring patients’ perceptions and experience of the procedure.

Data quality and qualitative rigour

Qualitative data are collected using open-ended prompts administered by a trained research nurse who is not involved in PICC/PICC-PORT insertion or intervention delivery.

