The qualitative component follows Van Kaam’s phenomenological method [18] both in data collection and analysis. Methodological rigour is supported through: (a) interviewer training in neutral and non-directive questioning; (b) reflexive documentation by the research team; (c) maintenance of an audit trail; and (d) regular analytic oversight to ensure consistency and transparency of interpretation, in accordance with established qualitative research criteria [23].

As all assessments take place during a single clinical encounter, no specific retention strategies are planned. The only potential source of missing data is interruption of the procedure for clinical reasons (e.g., patient distress or technical failure), which will be documented and reported in the CONSORT flow diagram.

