### 2.10. Data Management Plan and Analysis

Study data will be entered into an electronic database in REDCap, used exclusively for data management and not for randomisation. All entered data will be pseudonymised, and access will be restricted to personnel specifically authorised for the study through dedicated password-protected accounts. The data will be stored on an institutional server of the study hospital and retained according to the relevant regulations. Identifiable information will be kept separate from research data, ensuring full confidentiality.

De-identified individual participant data, the data dictionary and the statistical code will be made available upon reasonable request to the Principal Investigator. No identifying information will be shared.

Given the minimal-risk nature of the study and its single-centre design, no formal monitoring of trial conduct is planned. The research team will oversee the study, protocol adherence and data collection as part of routine clinical practice.

All analyses will be conducted according to the intention-to-treat (ITT) principle. Descriptive statistics will be used to summarise participants’ demographic and clinical characteristics. Continuous variables will be reported as means and standard deviations or medians and interquartile ranges, as appropriate, according to variable distribution, while categorical variables will be presented as frequencies and percentages.

For the primary composite outcome, between-group comparisons will focus on procedural anxiety (VAS-A) as the prespecified principal quantitative driver of the composite endpoint. Independent samples Student’s *t*-tests, or non-parametric equivalents when appropriate, will be used for between-group analyses. Patient-reported comfort, satisfaction and procedural tolerability will be analysed as individual, non-aggregated component dimensions of the composite endpoint using appropriate parametric or non-parametric methods and interpreted jointly with anxiety. Secondary quantitative outcomes, including procedural pain and physiological parameters, will be analysed using similar inferential methods.

Within-group pre- and post-procedural comparisons will be explored using paired statistical tests. Statistical significance will be set at a two-sided *p* < 0.05.

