The planned sample size is based on a power-based rationale focusing on procedural anxiety as the principal quantitative driver of the primary composite outcome. Assuming a clinically relevant between-group difference of approximately 1.5 points on a 10-point VAS-A, a standard deviation of 2.5, a two-sided alpha level of 0.05 and 80% power, a minimum of 44 participants per group is required. To account for uncertainty in effect size estimates, anticipated variability in a real-world clinical context and potential missing data or protocol deviations, the target sample size was increased conservatively to approximately 120 participants, consistent with the trial registration.

Missing data will be handled using complete-case analysis. If the proportion of missing data exceeds 10% for any key variable, sensitivity analyses may be performed to assess the robustness of the results.

No formal multivariable adjustment is planned, in line with the exploratory and pragmatic nature of the trial and the sample size, which is powered for the anxiety-driven component of the primary outcome. Potential confounders (e.g., baseline anxiety, pharmacological therapies and clinical context) are prospectively collected to support informed interpretation of outcome variability rather than formal statistical adjustment.

The study team will perform periodic internal monitoring of data completeness and protocol adherence using REDCap audit trails.

Qualitative data will be analysed using Van Kaam’s phenomenological method [18], involving systematic coding, identification of recurring themes and synthesis of the essential meanings of patients’ lived experiences. Quantitative and qualitative findings will be integrated at the interpretation stage using a narrative approach, whereby qualitative themes are used to contextualise and deepen understanding of the quantitative results. No formal mixed-methods integration techniques (e.g., data transformation or joint displays) are planned, given the protocol focus and exploratory aims of the qualitative component. Statistical analyses will be conducted using dedicated statistical software.

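### Patients whose procedure is interrupted, including for distress, have no defined T1 assessment and leave the complete-case primary analysis, with only an optional sensitivity analysis behind it

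*Protocol article*

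**What the plan says.** Four statements in the protocol article bear on this.

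- Cause of missing data (Section 2.8): "The only potential source of missing data is interruption of the procedure for clinical reasons (e.g., patient distress or technical failure". The same sentence adds that interruptions will be documented and shown in the CONSORT flow diagram.
- Timing of the outcome (Section 2.8): "T1 (post-procedural): within 2 min of completion of the procedure". No assessment time is given for a procedure that is stopped before completion.
- Handling (Section 2.10): "Missing data will be handled using complete-case analysis". Then: "If the proportion of missing data exceeds 10% for any key variable, sensitivity analyses may be performed". No method is named.
- Analysis principle (Section 2.10): "All analyses will be conducted according to the intention-to-treat (ITT) principle".

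On the primary outcome, Section 2.10 says that "between-group comparisons will focus on procedural anxiety (VAS-A) as the prespecified principal quantitative driver of the composite endpoint". Section 2.7 also places tolerability among the components of the primary endpoint. Baseline anxiety is recorded, but Section 2.10 plans no formal adjustment for it.

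**The concern.** Read together, these statements mean that a patient whose procedure is stopped has no defined T1 score and is left out of the primary comparison. When the reason is distress, the missingness is plausibly related to the outcome itself: such a patient would be expected to report high anxiety and poor tolerability. Complete-case analysis estimates the effect in all randomised patients without bias only if those lost do not distort the comparison between arms, and the stated cause of loss gives reason to doubt that.

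The 10% trigger does not protect against this. It looks at the quantity missing, whereas bias depends on the imbalance between arms and on the scores of those lost. Even above 10% the further analysis is discretionary. If VR changes how often procedures are stopped for distress, the VAS-A difference among completers is not the difference among those randomised.

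**Working it through.** **Inputs from Section 2.10.** The target difference: "Assuming a clinically relevant between-group difference of approximately 1.5 points on a 10-point VAS-A". The other design values: "a standard deviation of 2.5, a two-sided alpha level of 0.05 and 80% power". The stated minimum is 44 per group and the target is about 120 in total, so about 60 per arm under 1:1 simple randomisation.

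**Inputs that are assumptions.** The article gives neither an interruption rate nor a score for interrupted patients. Let q be the share of an arm lost, and D the amount by which the mean of those lost exceeds the mean of completers, on the scale analysed. D = 4 is used below, with a range of 2.5 to 5.

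**Step 1: the plan's own figure.** n per group = 2 × [2.5 × (1.960 + 0.842) / 1.5]² = 43.6, rounded up to 44. The stated figure reproduces.

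**Step 2: is power the problem?** No. By the normal approximation, power is 90.8% with 60 per arm, 87.7% with 54 (10% lost) and 80.4% with 44 (27% lost).

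**Step 3: bias.** In one arm, the mean of all randomised = (1 − q) × completer mean + q × (completer mean + D) = completer mean + qD. Completers therefore understate that arm's mean by qD. For the difference VR minus SOC:

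bias = −(q_VR × D_VR − q_SOC × D_SOC)

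A negative value favours VR. With equal q and equal D the bias is zero. With equal D it reduces in size to (difference in loss) × D.

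| Loss, one arm vs the other | Overall loss | Bias at D = 4 | Share of 1.5 |
|---|---|---|---|
| equal rates, equal D | any | 0 | 0% |
| 1 of 60 vs 0 | 0.8% | 4/60 = 0.07 | 4% |
| 10% vs 5% | 7.5% | 0.05 × 4 = 0.20 | 13% |
| 10% vs 3% | 6.5% | 0.07 × 4 = 0.28 | 19% |
| 10% vs 0% | 5% | 0.10 × 4 = 0.40 | 27% |
| 12 of 60 vs 0 | 10% | 0.20 × 4 = 0.80 | 53% |

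Over D = 2.5 to 5, the 10% vs 5% case gives 0.125 to 0.25 points (8–17%), and the 10% vs 0% case gives 0.25 to 0.50 points (17–33%).

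**Step 4: the trigger.** Taken over both arms, 12 of 120 is exactly 10% and does not exceed it. None of the rows with unequal loss would prompt even the optional sensitivity analysis.

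**Step 5: type I error.** With no true effect, D = 4, SD 2.5 and 60 randomised per arm:

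- 10% vs 5% lost leaves 54 and 57 patients. SE = 2.5 × √(1/54 + 1/57) = 0.475 and bias/SE = 0.42, so the two-sided error is about 7%.
- 10% vs 0% lost leaves 54 and 60 patients. SE = 0.469 and bias/SE = 0.85, so the error is about 14%.

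**The case against.** The other side has real force, and several of its points limit the conclusion.

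- **Who is lost.** A reader might infer that the rule removes precisely the most anxious patients. The article does not say so. Distress is one of two examples, technical failure has no stated link to anxiety, and high scores among those interrupted are an inference.
- **Visibility.** A reader might infer that interruptions would be concealed. They would not: Section 2.8 commits to reporting them in the flow diagram. But reporting the count does not correct the estimate.
- **Headset intolerance.** It is tempting to count patients who cannot tolerate the headset as lost. Section 2.6.1 says that if the device is removed the procedure carries on under standard care, so these patients can still reach T1.
- **Size.** The Introduction describes the procedure as minimally invasive with usually mild pain, so interruptions may be rare. The 0.80-point case needs a fifth of one arm stopped and none of the other. Section 2.7 also frames anxiety as change. If distress-prone patients start higher, their excess in change could be smaller than their excess at T1.
- **Direction.** If VR reduces distress, loss falls mainly on SOC and the bias works against VR, which is conservative in a superiority trial.
- **The ITT label.** Analysing patients as randomised with observed outcomes is a common use of the term, and the handling of missing data is stated openly. This is a tension more than a flat contradiction.
- **Detail left to an analysis plan.** The choice of sensitivity method can properly be left to a document not shown. The article itself, however, fixes complete-case handling, the optional 10% trigger and T1 timed from completion.

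Neither the larger sample nor the recorded baseline anxiety answers the core point. The first protects power, and the second is not used for adjustment.

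**Conclusion.** The concern holds in a limited form. By the plan's own account, data go missing through interruption, which includes interruption for distress. T1 is not defined for those patients, and the stated rule drops them from analyses of outcomes plausibly related to the reason for loss. The only safeguard is optional and tied to a percentage that does not measure the risk.

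The size is not known. With a 4-point excess it runs from about 0.07 points for one extra interruption in an arm, through 0.28 points at 10% vs 3% loss, to 0.80 points as an extreme bound. It is zero when loss and severity are equal in the two arms. More distress interruptions under SOC would work against VR, and more under VR would favour it. The article does not support a claim that the result will be biased, or biased in VR's favour. It supports the narrower claim that the plan leaves an avoidable route to bias open and commits to no check on it. The change should be made, but the gap does not undermine the trial.

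**What to change.** 1. In Section 2.8, define T1 as within 2 minutes of completion or interruption of the procedure, and attempt VAS-A and the other ratings then in every randomised patient able to give them. The article does not say that the research nurse is present throughout, so the team should confirm who collects the ratings when a procedure stops early.
2. In Section 2.10, replace the optional 10% trigger with a prespecified sensitivity analysis for any T1 still missing, run whatever the percentage and allowing for data missing not at random. One suitable form is delta-adjusted imputation by arm using baseline VAS-A. Assigning the worst score to distress interruptions can serve as one bound, but should not be the only method, since it can introduce a difference between arms of its own.
3. Report interruptions by arm and reason beside the primary result.

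The cost is one sentence in the T1 definition and one short extra analysis, with no added visits. All assessments fall in a single encounter, so a score missed at T1 has no later planned assessment. The change is therefore worth making promptly.

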## 3. Ethical Considerations

The study is conducted in accordance with the principles of the Declaration of Helsinki. All participants provide written informed consent prior to enrolment, after receiving comprehensive information about the study from trained members of the study team, and are informed of their right to withdraw from the study at any time without consequences for their standard clinical care.

The study protocol, including all amended documents, has been reviewed and approved by the Comitato Etico Territoriale Area Nord Veneto (CET-ANV). Following submission and evaluation of the requested amendments, the Ethics Committee issued a final favourable opinion (internal code CET-ANV 2025-18, Version 1.0, dated 5 September 2025) authorising the conduct of the study.

Any protocol amendments will be communicated to the Ethics Committee and updated in the trial registry (ClinicalTrials.gov).

Study results will be disseminated through publication in peer-reviewed journals, presentations at scientific conferences and summary reports provided to participants upon request.

The virtual reality device complies with European medical device regulation and does not involve acquisition, storage or processing of patient data, therefore posing no additional risks in terms of data protection or privacy for study participants.

A Data Monitoring Committee (DMC) is not planned for this study, given the minimal risk of the intervention, which does not involve the use of drugs, and its complementary nature to routine clinical procedures. No additional risks beyond standard clinical procedures are anticipated.

Given the minimal risk of the intervention, no ancillary post-intervention care is planned. Participants will continue to receive standard care according to institutional clinical protocols.

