## 1. Introduction

After recent advances in virtual reality (VR), this technology has been adopted in healthcare for a range of interventions, from clinical training and rehabilitation to mental health and pain management. VR systems offer an immersive and multisensory experience capable of capturing patients’ attention and potentially affecting their perception of medical procedures.

Recent studies have shown that, compared with conventional distraction techniques, VR has proven more successful in modulating pain and anxiety during clinical procedures by redirecting the patient’s focus towards engaging, calming environments and potentially influencing the neuromatrix of pain and anxiogenic input [1]. This process is thought to reduce the subject’s perception of discomfort and promote a state of relaxation and emotional containment [2,3,4]. Given that the side effects of virtual reality are generally mild, primarily including dizziness or nausea, often referred to as cybersickness [5,6], VR is considered a feasible and beneficial complement to standard care under local anaesthesia.

To date, the paediatric population has generated the most data supporting VR use in clinical settings [7], while adult patients undergoing invasive procedures are less studied. Nonetheless, recent studies in adult settings suggest that the use of VR may result in a reduction in procedural pain and anxiety without modifying or prolonging the duration of the procedure or increasing pharmacological sedation [3]. However, these studies are largely focused on the use of virtual reality in surgical settings; indeed, the recent meta-analysis by Lassen et al. [3] includes 37 articles, the majority of which were conducted in operative contexts, and only three investigate the use of VR during the insertion of central venous access devices (CVADs), which is the focus of the present protocol paper.

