### 2.6. Intervention

#### 2.6.1. Virtual Reality Plus Standard of Care (Vr + Soc)

Participants allocated to the intervention group undergo PICC or PICC-PORT placement according to institutional standard procedures, combined with the use of an immersive virtual reality system delivered via a head-mounted display during the procedure.

The VR system used is a commercially available Class I non-sterile medical device, compliant with EU Regulation 2017/745 (Medical Device Regulation) [21]. The device delivers immersive audiovisual content, integrating visual environments, guided breathing, and structured audio designed to promote relaxation and attentional engagement. See Supplementary Materials File S1, for further technical information.

The VR device does not record, store or transmit any personal or clinical data, and its use does not involve data processing activities beyond content visualisation. Prior to the procedure, patients may select among different visual and audio environments. Throughout the intervention, verbal interaction with healthcare professionals is continuously maintained, assuring safety and preserving the usual communicative flow of the procedure.

The VR intervention is implemented exclusively as a supportive, non-pharmacological adjunct to standard care and does not replace clinical communication, procedural monitoring or operator–patient interaction during device placement. All standard clinical care procedures are permitted and are not altered by the intervention. In the case of cybersickness or clinically relevant symptoms such as nausea, dizziness or visual discomfort, the operator is ready to assess and intervene, including removing the VR device if necessary. In such cases, the procedure continues according to standard care.

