### 2.7. Outcomes

The primary outcome of the study is a composite patient-reported procedural experience endpoint, reflecting the overall effectiveness of the virtual reality intervention during PICC and PICC-PORT placement. Although the term “composite endpoint” is used, it refers here to a conceptual and experiential framework rather than to a statistically aggregated outcome.

This composite endpoint integrates multiple dimensions of procedural experience, including:change in procedural anxiety, which represents the prespecified principal quantitative driver of the endpoint;patient-reported comfort and satisfaction with the procedure;perceived procedural acceptability and overall tolerability.

Procedural experience is assessed immediately after completion of the procedure (T1) using structured patient-reported measures, combining ordinal rating scales and qualitative evaluation to assess complementary quantitative and experiential elements. Procedural anxiety (measured using the 10-point Visual Analogue Scale for Anxiety, VAS-A) constitutes the primary focus of analysis, while the remaining component dimensions (comfort, satisfaction and procedural tolerability) are analysed as individual, non-aggregated measures and interpreted jointly with anxiety to provide an overall understanding of procedural experience. No numerical aggregation of component scores is applied.

This approach reflects the multidimensional and subjective nature of immersive digital interventions, for which patient experience constitutes a clinically meaningful outcome.

Secondary outcomes include:procedural pain, assessed using a 10-point Visual Analogue Scale (VAS);physiological parameters, including heart rate and systolic, diastolic and mean arterial pressure as routinely monitored;procedural characteristics, including procedure duration and number of insertion attempts;qualitative assessment of patients’ perceptions and lived experiences related to the procedure, analysed using Van Kaam’s phenomenological method [18].

This exploratory analysis aims to elucidate the relationship between procedural anxiety and the other experiential dimensions and to facilitate comparison with previous studies in which anxiety was evaluated as a standalone outcome. Procedural pain and anxiety are therefore analysed separately to explore their individual contributions to the overall procedural experience.

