From a clinical perspective, this trial evaluates VR as a complementary, non-pharmacological intervention designed to enhance, not replace, established protocols. We conceptualize VR strictly as a supplement to standard care rather than a substitute for analgesic therapy or human interaction. Ultimately, if proven beneficial, VR offers a scalable, low-risk strategy to improve patient experience during routine oncological procedures.

Despite its methodological strengths, the trial presents anticipated limitations. Although the planned sample size is adequate for detecting moderate effects and assessing the primary exploratory objectives of the study, it may not be sufficient to identify subtle differences, particularly for secondary quantitative outcomes. However, the sampling strategy and planned sample size are appropriate for an exploratory, pragmatic, single-centre randomized trial and are sufficient to generate clinically meaningful estimates for the anxiety-driven component of the primary composite endpoint.

Moreover, while integrating both quantitative and qualitative criteria is a methodological strength, patient-reported parameters naturally increase statistical variability. This inherent variance can complicate the interpretation of outcomes. Furthermore, the single-centre design may limit generalizability, as institutional care pathways and patient characteristics may vary across oncology settings.

In addition, the pragmatic, unblinded design represents an inherent limitation. Given the reliance on patient-reported outcomes, expectation or performance bias cannot be excluded and should be considered when interpreting effect estimates. However, patient awareness of the intervention reflects real-world clinical practice and constitutes a meaningful component of the experiential effect of immersive VR.

Nevertheless, the consecutive recruitment of a real-world clinical population and full alignment with prospective trial registration support the internal validity of the findings and enhance their relevance to routine clinical practice. These aspects should be taken into account when interpreting the results and planning future confirmatory studies.

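### Headset-related symptoms and early headset removal are foreseen but not counted by any named outcome, while the ethics section anticipates no added risk

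*Protocol article*

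**What the plan says.** **Foreseen effects.** The Introduction says that "side effects of virtual reality are generally mild, primarily including dizziness or nausea, often referred to as cybersickness". Section 2.6.1 carries this into the trial: "In the case of cybersickness or clinically relevant symptoms such as nausea, dizziness or visual discomfort, the operator is ready to assess and intervene". Taking the headset off is one of the responses it foresees, after which the procedure goes on under standard care. Section 2.6.3 has VR patients told how to report discomfort quickly.

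**Stated risk.** The paragraph of Section 3 that explains why there is no data monitoring committee describes the intervention's risk as minimal and ends: "No additional risks beyond standard clinical procedures are anticipated".

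**Outcomes and data items.** The primary composite (Section 2.7) covers anxiety, comfort, satisfaction, and acceptability and tolerability. The secondary outcomes are pain, heart rate and blood pressure, "procedural characteristics, including procedure duration and number of insertion attempts", and a qualitative assessment. Section 2.9.1 adds a descriptive record of the local anaesthetic. Section 2.8 documents interruption of the procedure for clinical reasons in the flow diagram.

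**Foreseen conclusion.** The Discussion says: "Ultimately, if proven beneficial, VR offers a scalable, low-risk strategy to improve patient experience during routine oncological procedures".

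**The concern.** There are two linked problems.

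First, the risk statements disagree. Symptoms that the article itself attributes to VR, and that may lead to the headset being taken off, are a risk that placement without a headset does not carry. A risk that is mild or minimal is still an additional one. Minimal risk is also the stated reason for having no data monitoring committee (Section 3) and, together with the single-centre design, no formal monitoring of trial conduct (Section 2.10).

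Second, the events that would test the low-risk description are not among the named outcomes or data items. The Discussion makes that description conditional on benefit alone. If the form follows the article's lists, the trial report could give mean tolerability by arm, but not how many VR patients felt sick or dizzy or how many had the headset removed. All assessments take place in one encounter, and Section 2.6.1 says that the device stores no personal or clinical data, so what is not recorded on the day may not be recoverable later.

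**Working it through.** **Step 1. Trace each foreseen event through the article.**

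| Place | Symptoms (nausea, dizziness, visual discomfort) | Early headset removal |
|---|---|---|
| Introduction | Dizziness and nausea named as side effects | Not mentioned |
| 2.6.1 Intervention | Foreseen | Foreseen |
| Outcomes and Aim; 2.7 Outcomes | Not listed | Not listed |
| 2.8 Data collection at T0 and T1 | Not listed | Not listed |
| 2.8 Event record | Only if the procedure is interrupted | Not covered when the procedure continues |
| 2.9.1 Measures | 5-point tolerability rating, not symptom-specific | Not listed |
| 2.10 Analysis | Not listed | Not listed |
| 3 Ethical Considerations | No additional risk anticipated | Not mentioned |

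A patient whose headset is removed and whose procedure is completed has T1 data and stays in the VR arm under intention-to-treat. Nothing in the event record described would mark that patient.

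**Step 2. The plan's own figure.** The only calculated figure is the sample size: n per group = 2 × (1.960 + 0.842)² × 2.5² / 1.5² = 43.6, so 44, which reproduces. It is not in dispute and does not bear on this point. The input used below is the target of about 120 with 1:1 allocation, so about 60 VR patients. Because randomisation is simple, 60 is an expected number and not a fixed one.

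**Step 3. What a count would provide.** With zero events in n patients, the exact upper limit is 1 − α^(1/n).

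- One-sided 95%, n = 60: 1 − 0.05^(1/60) = 4.9%.
- Two-sided 95%, n = 60: 1 − 0.025^(1/60) = 6.0%.
- Two-sided 95%, n = 44 (the plan's minimum per group): 1 − 0.025^(1/44) = 8.0%.

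If 3 of 60 had an event (5.0%), the exact 95% interval would be 1.0% to 13.9%.

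**Step 4. Would events be seen at all?** The documents give no expected rate, so the rates here are assumptions. The chance of at least one event in 60 is 1 − (1 − p)^60:

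| Assumed true rate | Chance of at least one event |
|---|---|
| 1% | 45% |
| 2% | 70% |
| 5% | 95% |
| 10% | 99.8% |

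A count in this trial would therefore be informative for rates of about 5% and above, and weak for rarer events.

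**The case against.** The strongest reply is that an article cannot prove an absence. Section 2.9.2 refers to the approved dataset in File S2, and Figure 1 is said to detail variables and time points. Neither is shown, and either may contain a symptom or removal field. This stands, so the point is confined to what the article names. A field on the form would still not be a stated outcome, and it would not settle the conflict between Section 3 and Section 2.6.1.

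A reader might infer that the trial will have no data on harm, or can report benefit but not harm. The documents do not support that. Tolerability, comfort, anxiety, pain, heart rate and blood pressure could all come out worse under VR; open-ended questions are asked at T1; and interrupted procedures are documented. These measures can show harm indirectly, but they do not give a count of symptoms or removals.

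A reader might also infer that a null intention-to-treat result would be uninterpretable because of non-use. That goes too far. In a pragmatic trial, intention-to-treat validly estimates the effect of offering VR, early removals included, and Section 2.10 plans internal checks of protocol adherence. A removal count would help to explain such a result; it is not needed to make it valid.

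It can also be said that the Section 3 sentence is loose wording next to minimal risk, and that the low-risk remark is a conditional comment in the Discussion and not an objective. Both are fair. They limit the weight of the point but do not remove it, since the sentence still disagrees with Section 2.6.1 and the remark still lacks a planned event rate behind it.

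**Conclusion.** The point holds in a limited form. The Introduction and Section 2.6.1 foresee effects specific to the headset, Section 3 anticipates none beyond standard procedures, and these statements must be reconciled. The article names no outcome or data item that counts the symptoms or early headset removal, and its one event record misses a removal after which the procedure continues. The foreseen low-risk statement would therefore rest on general tolerability ratings and indirect measures.

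The size is what a count would add: with about 60 VR patients and zero events, a two-sided 95% upper limit of about 6.0% (4.9% one-sided). This assumes an arm close to its expected size and a complete record in every VR patient. It also assumes that the unseen supplementary files do not already define such an outcome.

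The primary comparison, the sample size and the intention-to-treat analysis are not affected. This is a worthwhile and inexpensive improvement, not a flaw that undermines the trial.

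**What to change.** 1. Name a descriptive secondary outcome: occurrence of nausea, dizziness and visual discomfort (yes/no each) in both arms, and early headset removal (yes/no, with reason) in the VR arm. Recording symptoms in both arms gives a comparison, since nausea or dizziness may also occur without a headset.
2. If File S2 already has these fields, use them and state them as an outcome. If not, add them to the T1 form.
3. Report counts and proportions with exact 95% confidence intervals by arm. No hypothesis test and no change in sample size are needed.
4. Reconcile the risk sentence in Section 3 with the Introduction and Section 2.6.1.
5. Limit any low-risk statement to what these data support, quoting the upper confidence limit.

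**Cost.** Three items for every patient and two more in the VR arm, within a T1 assessment that is set within two minutes of the end of the procedure and already holds several scales and open questions. A change to the protocol also means notifying the ethics committee and updating the registry, as Section 3 provides. The changes above alter no clinical procedure.
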